## Participant safety monitoring

The study itself does not provide treatments of any kind. No products, medications or tests are being delivered as part of this study, though relatives are offered optional genetic testing services through the Program platform, and these are delivered by a third party, Color Health, for interested relatives. Identified potential risks to human subjects for this study include: (1) breach of confidentiality of PII and/or protected health information (PHI); (2) negative patient or relative reactions to study procedures; and (3) relatives’ difficulties dealing with the results of genetic testing received through Color Genomics as part of the FGHP.

The Leadership Team engages regularly with an appointed Data and Safety Monitoring Committee (DSMC) to monitor progress and benchmarks of the study. The DSMC is a multidisciplinary committee at the Rogel Cancer Center responsible for monitoring the safety and data integrity of appropriate cancer clinical research protocols conducted at the University of Michigan. The DSMC (1) reviews accrual information and determine whether and to whom outcome results should be released prior to the reporting of study results; (2) reviews reports of related studies to determine whether the monitored study needs to be changed or terminated; (3) reviews major proposed modifications to the study prior to their implementation (e.g., termination, dropping an arm based on reported trial outcomes, increasing target sample size); and (4) provides the Leadership Team with written information concerning findings for the trial as a whole related to cumulative adverse events observed and any relevant recommendations related to continuing, changing, or terminating the trial. A copy of this information will be provided to the NCI Division Director or designee. The Leadership Team provides information on cumulative adverse events and relevant recommendations to the local principal investigators to be shared with their IRBs.

## Adverse event management

We have been attentive to ensuring that there are processes in place to address any adverse events for participants in this study. Participation for both patients and relatives is completely voluntary, including the offer of genetic testing to relatives via Color Health. We collaborate closely with our partners at Stanford University and the SEER registries as well as the DSMC to proactively address any possible concerns. Any adverse events or unanticipated problems that do occur are discussed via the monthly Leadership Team meeting and/or the weekly team meetings. Participant confidentiality is always maintained. These events are recorded by the relevant site PI and reported to all IRBs of record and to the study sponsor. This is done by first submitting an “adverse event” amendment form to the UM IRB per protocol, followed by submission of similar forms to the other IRBs. Should any adverse events appear to be occurring frequently, we will amend the protocol to address these concerns. We do not anticipate having to stop the trial for these types of adverse events should they occur.

## Subject accrual and compliance

Review of the rate of subject accrual and compliance with inclusion/exclusion criteria occurs bi-weekly to monitor accrual progress. The DSMC reviews interim analyses of accrual and outcome data that are prepared by the analytic team and makes recommendations whether the study needs to be continued, changed, or terminated. In addition, the DSMC review and approve major modifications to studies that are proposed by the study team. All DSMC recommendations for study closure or study design changes are forwarded to the NCI for review and approval. In addition, the DSMC authorizes release of study data results. Progress reports, including patient and relative recruitment and retention/attrition are provided to the DSMC every three months. An annual quality assurance audit is conducted by the Quality Assurance Review Committee (QARC). QARC provides assurance that the trial is conducted, and data are collected, documented, and reported in compliance with the protocol and Good Clinical Practice Guidelines (GCP). The Annual Report is sent to the DSMC and is forwarded to the IRB and study sponsor. The IRB and other applicable recipients review progress of this study on an annual basis. The Contact PI ([name]) also sends copies of signed recommendations and comments from the DSMC to the sponsor Program Officer within one month of each monitoring review.

### Analysis plan

The analysis plan remains unchanged at the end of enrollment from that described in our IRB filing of 10/28/22 at the start of enrollment (see Study Protocol in Supplemental Material). As described above, we are testing the main effects of two interventions, represented by the separate platform design features of reduced vs. free test cost and web-based vs. human navigator communication and decision support. The 2 × 2 factorial design with block randomization at the level of the index patient (j) results in four groups of index patients of equal size. There are several analytic issues common to the primary and two secondary aims.

First, we do not hypothesize that there will be any synergistic effect of the two treatments on the log odds scale and thus assume that the effects will be additive. Conceptually we cannot think of any reason that the effect of the cost of the testing and any help provided by a navigator over the website have an obvious reason to be dependent on the level of the other. Thus, our primary outcome for the primary and secondary aims is the treatment effect of each intervention in a regression model without an interaction term.

The second analytic issue is that of informative cluster size. An assumption of the generalized linear multilevel models used in our analysis is that cluster size is not informative. The literature on family communication does not generally talk about family size as one of the factors that predicts health communication but there is little data one way or the other looking specifically at genetic testing. Thus, there is little to guide us on whether larger families are more or less likely to communicate well, or be likely to invite relatives, or whether relatives in larger families are more or less likely to get genetic testing when there is a potential health benefit. Thus, given the conditional independence assumption we will condition the models on cluster size with a threshold of including this covariate as a p value of 0.10 or less.

Finally, some of our analytic models will have other covariates including cluster size noted above and in some cases baseline levels of the outcome variable for models estimating change from a baseline variable. All of our models will include the stratification design variable for site (CA vs. GA). For models that include covariates we will estimate the marginal main effect of each treatment by averaging over the distribution of the covariates included in each model (such as baseline levels of outcome variables, state or cluster size). This in effect standardizes the treatment effect to a population with the distribution of those covariates observed in our study sample. For generalization purposes we have a fully population-based sample drawn from SEER registries. Thus, the baseline distribution of non-treatment covariates in our study sample is directly generalizable to the index patient population of the two large states from which the sample is drawn who are willing to enroll in a program to increase informed family participation in genetic testing. This is the target population of interest for any broader program that could be developed if the trial is successful.

Analysis plan for the Primary Aim (Family Genetic Testing Fraction), the dependent variable is the number of relatives who complete genetic testing from Color using a study-provided token. This outcome is the pre-specified primary outcome of the trial. We will describe a “*Family Genetic Testing Fraction*” as the proportion of eligible relatives of a patient who complete genetic testing. We anticipate that zero cost of the test and increased navigation support will be associated with a greater proportion of relatives completing testing, as quantified by the coefficients and standard errors of these covariates. For the Primary Aim, the target population is all eligible relatives who are identified by the index subject. The intervention is randomized by the index patient. We approach relatives only through the index patient, who will have an influence on the relatives’ responses based at a minimum on their prior relationship and most likely with direct communication about the study. Thus, the analysis for this Primary Aim will account for the cluster level randomization of the intervention and nesting of relatives within each index patient using multilevel generalized linear models. We will use a multilevel binomial regression model with a random intercept estimated for each index patient, the number of successes (relatives who are tested) as the outcome and the number of trials set as the number of eligible relatives. We will include the number of eligible relatives as a covariate in the model if the coefficient is significant (at the *p* = 0.10 level). We will also include relative sex and the patient-reported assessment of communication with family scale score to improve power as these baseline variables are likely to predict the outcome. No other variables will be included. The main effects of each intervention will be quantified by the marginal effect of the respective treatment variable averaging across the other treatment variable, covariates and cluster (eligible family) size.

For Secondary Aim 1 (Family Invite Fraction), the dependent variable is the number of a patient’s total eligible relatives for whom the patient is willing to provide contact information given the total number of eligible relatives (“*Family Invite Fraction*”). We expect that zero cost and increased navigation help will be associated with an increase in the proportion of relatives for whom a patient is willing to provide contact information, quantified by the coefficients and standard errors of these variables. We will use a multilevel binomial regression model with a random intercept estimated for each index patient, the number of successes (family members for whom an address is provided) as the outcome and the number of trials set as the number of eligible relatives. We will include the number of eligible relatives as a covariate in the model if the coefficient is significant (at the *p* = 0.10 level). We will also consider including the scale score of patient report of assessment of communication with family collected on the baseline PICS survey to improve power. No other variables will be included. The main effects of each intervention will be quantified by the marginal effect of each treatment variable averaging across the included covariates.

For Secondary Aim 2 (Assessment of Family Communication Scale), the target population of the intervention is the index cancer patient. The analytic sample includes all patients who consent and are randomized (expected *n* = 412). The dependent variable is the patient’s assessment of their communication with relatives (“*Patient assessment of family communication about genetic testing”)* at six-month follow-up, which will be measured as a continuous outcome using a multi-item scale. The treatment effect represents the change in assessment score from baseline to follow-up. We anticipate that increases in mean assessment score will be associated with zero cost and genetic risk navigation help. We will use linear regression to estimate the main effects of cost reduction and navigator help included as two treatment (1/0) variables. Each index patient’s baseline assessment score will be included as a covariate. We will include cluster size as a covariate if the coefficient is significant at the 0.10 level. The main effects of each intervention will be quantified by the marginal effect of each treatment variable averaging across the included covariates. The standard error of the main effect will define the confidence interval for the intervention effect.

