#### Navigator invitation

Patients in Arms 3 and 4 can also ask the Family Health Navigator to help invite their relatives. Whether or not to involve the Navigator is on a per-relative basis. If the patient chooses Navigator invitation, they will also be asked to provide a phone number for that relative.

Relatives who have been invited with Navigator assistance receive email reminders encouraging enrollment as described above. In addition, the Navigator supplements these auto-emails with phone calls and/or personal emails to encourage enrollment. The Navigator routinely monitors the project dashboard and will not follow up with relatives who have already enrolled.

Regardless of study arm, all invited Relatives eventually receive an Invitation Email containing a clickable link to the GIFT Study website and the Relative’s unique Access Code. The study is described to relatives according to the family’s randomization assignment (study arm) and the fact of randomization assignment is concealed. Both patients and the Navigator can re-send email invitations as needed.

We expect that patient participants in the study (*N* = 412) will have on average a total of eight first-degree (biological parent, sibling, or biological child) and/or second-degree (biological aunt, uncle, nephew, niece, grandparent, or grandchild) adult relatives and that patients will be willing to provide contact information (email address) for three of those relatives (*N* = 1236).

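### Family size enters the primary, Secondary Aim 1 and Secondary Aim 2 models only if its coefficient reaches p ≤ 0.10, so outcome data choose the adjustment set; it can be included always at no cost

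*Protocol article*

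**What the plan says.** The Analysis plan section of the protocol article raises informative cluster size as an issue common to its models: "An assumption of the generalized linear multilevel models used in our analysis is that cluster size is not informative". On the evidence it is open: "Thus, there is little to guide us on whether larger families are more or less likely to communicate well". Its answer is that "we will condition the models on cluster size with a threshold of including this covariate as a p value of 0.10 or less".

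The aim-specific paragraphs apply the rule:

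- **Primary Aim (Family Genetic Testing Fraction).** "We will use a multilevel binomial regression model with a random intercept estimated for each index patient", with eligible relatives as the number of trials. Then: "We will include the number of eligible relatives as a covariate in the model if the coefficient is significant", at the 0.10 level. Relative sex and the communication score are included without condition. The main effect is to be averaged over the other treatment, the covariates and family size.
- **Secondary Aim 1 (Family Invite Fraction).** The same rule for size. For the communication score: "We will also consider including the scale score of patient report of assessment of communication with family".
- **Secondary Aim 2 (communication scale, linear regression).** "We will include cluster size as a covariate if the coefficient is significant at the 0.10 level".

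The section states that the analysis plan is unchanged since the October 2022 filing, so the rule is in force. Secondary Aim 3 has no model in the article and is not part of this point.

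**The concern.** A significance test on the trial's own outcome decides whether a baseline quantity belongs in the model. This has three consequences.

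- **The response does not follow from the premise.** If it is unknown whether size matters, missing the 0.10 threshold does not show that it does not. Unconditional inclusion is the choice that needs no prior knowledge.
- **The primary model is not fixed.** Two different models can become the primary analysis, and the outcome data pick between them.
- **The estimand wording and the rule do not fit together.** The Primary Aim averages the effect over family size, while the same paragraph may leave size out. The general text averages over whichever covariates each model contains, so what is averaged over changes with the pre-test.

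Secondary Aim 1 has an extra looseness. The primary model commits to the baseline communication score, whereas Aim 1 only contemplates it and gives no criterion.

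**Working it through.** **Inputs from the article.** 412 enrolled patients (Table 2); median of 8 eligible relatives, ICC 0.15 and testing rates of 10%, 15%, 13% and 18% (Assumptions and Table 5); alpha 0.05 (Sample size calculations; two-sided assumed, as sidedness is not stated); stated power 0.80 at an odds ratio of 1.5 with 400 or more patients.

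**Step 1: reproduce the stated power.** Effective relatives per half of the trial = (400/2) × 8 / (1 + 7 × 0.15) = 1600 / 2.05 = 780. With p2 = 1.5·p1 / (1 − p1 + 1.5·p1) and a two-proportion test:

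- p1 = (10% + 13%)/2 = 11.5% gives p2 = 16.3%, power 0.785.
- p1 = (10% + 15%)/2 = 12.5% gives p2 = 17.6%, power 0.812.
- p1 = 10% (reference cell alone) gives p2 = 14.3%, power 0.737.

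The stated 0.80 is reproduced within 2 points from the averaged base rates.

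**Step 2: simulate the rule.** The random-intercept binomial model was fitted to 412 families, with latent-scale ICC 0.15, the second factor at odds ratio 1.4 and a site term. There were 1,200 runs per scenario with Wald tests. Further assumptions: family size is 1 + negative binomial with mean about 8.5, because the article gives no distribution; the size effects below are chosen for illustration; relative sex and the communication score are left out. Monte Carlo standard errors are √(0.05 × 0.95/1200) = 0.006 for type I error and √(0.8 × 0.2/1200) = 0.012 for power.

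| Assumed size effect on the log-odds | Size enters under the rule (no effect / OR 1.5) | Power at OR 1.5: never / always / rule | Type I error: never / always / rule | Verdict differs, with vs without size (no effect / OR 1.5) |
|---|---|---|---|---|
| none | 0.109 / 0.103 | 0.821 / 0.822 / 0.819 | 0.062 / 0.060 / 0.062 | 0.5% / 0.4% |
| −0.03 per relative | 0.728 / 0.773 | 0.820 / 0.820 / 0.819 | 0.063 / 0.064 / 0.062 | 1.4% / 2.7% |
| −0.06 per relative | 0.998 / 0.998 | 0.790 / 0.812 / 0.812 | 0.055 / 0.059 / 0.059 | 2.2% / 5.2% |
| odds proportional to 1/size (sizes below 3 set to 3) | 1.000 / 1.000 | 0.770 / 0.807 / 0.807 | 0.063 / 0.058 / 0.058 | 3.4% / 8.6% |

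**Step 3: read the table.**

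- Under modest dependence the rule omits a real size effect in 1 − 0.773 = 23% to 1 − 0.728 = 27% of trials.
- Power under the rule is within 0.003 of power with size always included, in every row. Type I error is within 0.002.
- The rule and unconditional inclusion can give different verdicts only in trials where size is dropped. The last column is therefore an upper limit for that disagreement: at most 2.7% at −0.03. At −0.06 the limit is 0.2%, because size is dropped in only 1 − 0.998 of trials.
- Always including size costs nothing visible when it has no effect (0.822 against 0.821 when it is never included).

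**The case against.** The rule is written down in advance: covariate, threshold and closure of the covariate list are all fixed, so the analyst has no discretion over family size. If dependence is strong, the test keeps size in 99.8–100% of simulated trials, which is the model asked for here. If dependence is weak, dropping size barely moves power or type I error. All of this stands. It limits the harm, but it does not fix which model is the primary one or reconcile the averaging statement with conditional inclusion.

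A reader might infer more than the documents support:

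- **That the fractions almost certainly fall with family size.** The Navigator invitation section expects eight relatives on average and says "patients will be willing to provide contact information (email address) for three of those relatives". Three invitations at every family size would give 3/4 = 75% in a family of four and 3/16 = 19% in a family of sixteen. But the three is an average, and the article does not say it is constant across family sizes. Four and sixteen are illustrative sizes, and the figure concerns invitations, not completed tests. Dependence is plausible but not established.
- **That the plan declares its model invalid if size is informative.** It names non-informative size as an assumption and offers a way of handling it.
- **That the rule loses power or inflates type I error.** The simulations do not show this.

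Secondary Aim 2 is a score per patient, not a fraction, so the denominator argument does not reach it. There the reason for change is consistency.

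**Conclusion.** The point holds as one of pre-specification and coherence. The plan lets outcome data choose the primary adjustment set, treats a non-significant test as an answer to a question it calls open, and defines an effect averaged over a variable that may not be in the model. It does not invalidate the planned tests.

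The size: under an assumed −0.03 log-odds per relative, a real size effect is left out in about a quarter of trials, with operating characteristics practically unchanged. These figures rest on an assumed family-size distribution and assumed size effects; the article gives neither. The non-committal wording on the communication score in Secondary Aim 1 is a smaller, related looseness. Together they are a free improvement.

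**What to change.** Before outcome data are analysed by arm:

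1. Delete the p = 0.10 rule from the general text and from the Primary Aim, Secondary Aim 1 and Secondary Aim 2 paragraphs.
2. Always include the number of eligible relatives in the primary and Secondary Aim 1 models, in a functional form stated in advance, and in Secondary Aim 2 for consistency.
3. In Secondary Aim 1, commit to the baseline communication score, as the primary model does.
4. Optionally, add a sensitivity analysis that weights each family equally.

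The cost is a few sentences and one degree of freedom per added covariate in about 412 families. In the two fraction models the number of relatives is already the binomial denominator, so using it as a covariate loses no further families. The Discussion says that invitation and enrollment of relatives were still ongoing. The section on subject accrual says the analytic team prepares interim outcome analyses for the monitoring committee, so the amendment should be dated and should state whether any outcomes by arm had been seen.

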### Sample size calculations

The number of enrolled subjects as achieved just prior to the close of enrollment was substantially lower than anticipated, however given considerable uncertainty in the planning stages about how successful our recruitment would be and the heterogeneity in the sample size requirements for the different aims, we had managed to design the trial such that the sample size for most of our aims were far larger than was needed to achieve a power of 0.8 with a alpha of 0.05.

Below we describe the calculations for power under the original and realized recruitment numbers.

For the primary aim we have two estimates, one for each of the two interventions in the factorial design.

### Assumptions

Effect sizes for the intervention were proposed to be the minimum clinically significant and achievable effect for assumed testing rates varying by trial features as shown in Table 5.

**Table 5 Tab5:** Minimally detectable absolute difference between study arms

	No Navigator	Navigator
$50	10%	15%
Free	13%	18%

These probabilities reflect odds ratios of 1.4–1.5. To account for clustering in the relatives’ outcomes at the patient level, we assumed an estimate of 0.15 for the residual intra-class correlation (after accounting for the intervention effects).

We originally hoped to enroll 880 index cancer patients with a median of 8 eligible relatives. As described in our original protocol, with these assumptions, a simulation based on our planned analytic approach confirmed a power of at least 0.80 for the effect of zero cost of the genetic test and navigation support for any effect including or above these specified effect sizes. However, we had built in a substantial buffer against our assumptions being different from what we proposed, including our enrollment numbers and the power was considerably higher than 0.80 for the larger sample size as seen in the graphs below and at an odds ratio of 1.5 we still have a power of 0.80 for the realized enrolled population of 400 or higher (Fig. 3).

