**Patients**	
Initial Patient Sample Selected	4,300 (approximate)
Respondents to PIC Survey	2,358 (expected response rate = 55%)
Pool of Patients eligible for GIFT Study Invitation	2,030 (86% of PIC survey respondents)
Patient GIFT Study Participants	412 (expected enrollment rate = 20%)

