
In summary, we view our experiences in this first large virtual intervention to deliver cascade cancer genetic risk education and testing in the community as a “glass half full”. Preliminary findings have shown that enrollees viewed their experiences favorably, but we did not achieve the participation we expected. The challenges we encountered are those that patients, families, and their clinicians face in practice every day. We have pinpointed the barriers to more robust uptake of the intervention, which will inform our next-generation intervention research: these include patients’ sense of the burden of obligation to contact relatives before being invited to our trial; patient reticence to re-visit prior informal and often clinically unsupported conversations with relatives; and the perception that the intervention has overemphasized an obligation to test vs. to deliver more effective cancer genetic risk education to relatives, so as to facilitate their shared decision-making about getting tested. However, as described in detail above, GIFT is sufficiently powered to detect clinically important differences across the study arms for the pre-specified primary and secondary outcomes. Our intervention experiences and outcomes inform strategies and tools to close the persistent gap in cascade genetic risk evaluation in families with hereditary cancer syndromes.

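### The retained 0.80 power at about 412 families applies to an odds ratio of 1.5; the planned cost effect in Table 5 is an odds ratio of 1.24 to 1.34 and has power of only about 0.41 to 0.57

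*Protocol article*

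**What the plan says.** All references are to the protocol article.

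- **Sample size calculations** sets the criterion as what is "needed to achieve a power of 0.8 with a alpha of 0.05" and says the primary aim yields two estimates, one for each randomized factor.
- **Assumptions, Table 5** (titled "Minimally detectable absolute difference between study arms") gives testing rates of 10% and 15% at $50 (without and with navigator) and 13% and 18% when the test is free. Their status is explicit: "Effect sizes for the intervention were proposed to be the minimum clinically significant and achievable effect". The next sentence reads: "These probabilities reflect odds ratios of 1.4–1.5".
- The same section takes a residual intra-class correlation (ICC) of 0.15 and an original target of "880 index cancer patients with a median of 8 eligible relatives", for which at least 0.80 power is claimed for both factors.
- Table 2 revises enrolment to "412 (expected enrollment rate = 20"%). For that level the text says "at an odds ratio of 1.5 we still have a power of 0.80 for the realized enrolled population of 400 or higher".
- **Discussion** concludes: "GIFT is sufficiently powered to detect clinically important differences across the study arms for the pre-specified primary and secondary outcomes".

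**The concern.** The stated odds-ratio range links the Table 5 rates to the power statement for the smaller trial. If every Table 5 effect were near 1.5, power of 0.80 at 1.5 would cover both factors, and the Discussion's conclusion would follow. Table 5 shows a 5-point navigator effect and a 3-point cost effect from similar base rates, so the two cannot share an odds ratio near 1.5. The power figure then speaks for the navigator only.

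At stake is how the cost result is read. If a 3-point effect is real and the design detects it about half the time, a non-significant result is the likely outcome in many repetitions. Set beside a statement that the trial was sufficiently powered, it could be taken as good evidence that a $50 charge does not deter testing.

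**Working it through.** **Inputs.** Families: 412 revised (Table 2), 400 in the article's own power statement, 880 original. Relatives per family: 8 (a median in the article, taken here as constant). ICC: 0.15. Allocation: four equal arms (Analysis plan), so half the families are at each level of each factor. Model: main effects only. Alpha: 0.05, assumed two-sided because the article does not say.

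**Step 1: odds ratios from Table 5.**

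| Contrast | Calculation | Odds ratio |
|---|---|---|
| Cost, no navigator | (0.13/0.87)/(0.10/0.90) | 1.34 |
| Cost, navigator | (0.18/0.82)/(0.15/0.85) | 1.24 |
| Navigator, $50 | (0.15/0.85)/(0.10/0.90) | 1.59 |
| Navigator, free | (0.18/0.82)/(0.13/0.87) | 1.47 |

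Averaged over the other factor, cost is 12.5% against 15.5% (odds ratio 1.28) and navigator is 11.5% against 16.5% (1.52).

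**Step 2: method.** Design effect = 1 + (8 − 1) × 0.15 = 2.05. Effective relatives per level n = (families/2) × 8 / 2.05. SE = √[(p₁(1−p₁) + p₂(1−p₂))/n]. Power = Φ((p₂ − p₁)/SE − 1.96).

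**Step 3: reproduce the article's figure.** For 400 families, n = 1,600/2.05 = 780. An odds ratio of 1.5 from 12.5% gives 17.6%. SE = 0.0181, z = 0.0515/0.0181 = 2.85, power = 0.81. This agrees with the stated 0.80.

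**Step 4: Table 5 effects at 412 families.** n = 1,648/2.05 = 804.

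- Navigator: SE = 0.0173, z = 0.05/0.0173 = 2.90, power = 0.83.
- Cost: SE = 0.0173, z = 0.03/0.0173 = 1.73, power = 0.41.

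**Step 5: sensitivity of the cost power at 412 families.** The article does not say on which scale the ICC of 0.15 is defined, so both were tried, by formula and by simulating the planned random-intercept binomial model (600 and 1,000 replicates).

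| Reading | Cost power |
|---|---|
| ICC on proportion scale, formula | 0.41 |
| ICC on proportion scale, simulation | 0.43 and 0.48 (two runs) |
| ICC on latent logit scale (about 0.066 as a proportion-scale ICC), formula | 0.54 |
| ICC on latent logit scale, simulation | 0.53 to 0.57 |
| One-sided 0.05, proportion scale, formula | 0.54 |
| No clustering at all (n = 1,648 per level): SE = 0.0121, z = 2.48 | 0.70 |

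Simulated navigator power was 0.83 to 0.93 over the two scales.

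**Step 6: detectable cost difference.** Solving for 80% power from 12.5% at 412 families gives 5.0 points (proportion scale) or 4.2 points (latent scale), against the 3 points in Table 5.

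**The case against.** - **ICC scale.** The original simulation is said to follow the planned random-intercept model, where a latent-scale ICC would be natural. On that scale the claim of at least 0.80 for cost with 880 families is right (0.85 to 0.87); on the proportion scale it is 0.71 to 0.75. This stands: the 880-family claim cannot be called wrong. The proportion scale does fit the article's 0.80 at 400 families better (0.81, against 0.87 to 0.92 simulated on the latent scale). At 412 families the cost effect is underpowered on either scale.
- **Marginal or conditional odds ratios.** The planned model estimates odds ratios conditional on family, while Step 1 gives marginal ones. With a latent ICC of 0.15 the conditional values are 1.27 to 1.37 for cost and 1.51 to 1.64 for navigator. Cost still lies below 1.4, but corrected text should name the scale.
- **Covariates.** The article expects uncounted efficiency from baseline measures. Removing all between-family correlation would still leave cost at 0.70.
- **Figure 3** was not visible here and may plot power at smaller odds ratios. A correct curve would not repair the odds-ratio sentence or the Discussion's conclusion.
- **Conditional wording.** The power sentence is openly tied to an odds ratio of 1.5 and reproduces, and Sample size calculations claims adequacy for most aims, not all. That is fair. The faults are the mislabelled range and the unqualified conclusion drawn from it.
- **Interpretation and severity.** Nothing commits the authors to reading a null as no effect, and the planned analysis already yields standard errors. Enrolment was about to close and the correction alters no procedure. These points limit the consequences; they do not make the statement true.

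**Conclusion.** The point holds. The stated odds-ratio range is wrong for both cost contrasts, and the sufficiency claim is unsupported for the planned 3-point cost effect. Power at 412 families is about 0.41 to 0.57, so the trial would miss that effect roughly 43% to 59% of the time. The navigator effect keeps at least 0.80.

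The result assumes a two-sided 0.05 test, a constant 8 relatives per family, an ICC of 0.15 and the Table 5 rates. Variable family size would tend to lower power further. Cost and navigator are two effect estimates on one primary outcome, so the shortfall affects half of the primary aim. Because that half carries a false statement of adequacy, it must be corrected.

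**What to change.** 1. Replace the odds-ratio range with 1.24 to 1.34 for cost and 1.47 to 1.59 for navigator, labelled as marginal; if family-conditional values are preferred, give those and say so.
2. State the scale of the ICC and whether the test is one- or two-sided.
3. Add a short table of power at 412 families for each factor at the Table 5 rates (about 0.83 or more for navigator, about 0.4 to 0.57 for cost), or state the cost difference detectable at 80% power (4.2 to 5.0 points).
4. Limit the Discussion's sufficiency statement so that it no longer covers the cost effect.
5. Commit now to interpreting the cost effect by its estimate and confidence interval, so that a non-significant result is not reported as evidence of no effect.

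The cost is revised text, one small table and a less favourable stated figure. No patients, procedures or analysis models change.
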